# Traditional Chinese medicine Lingguizhugan decoction treating non-alcoholic fatty liver disease with spleen-yang deficiency pattern: Study protocol for a multicenter randomized controlled trial

**DOI:** 10.1186/s13063-020-04362-7

**Published:** 2020-06-10

**Keywords:** Non-alcoholic fatty liver disease, Traditional Chinese medicine, Lingguizhugan decoction, Randomized controlled trial

## Abstract

**Background:**

Non-alcoholic fatty liver disease (NAFLD) is a common chronic liver disease characterized by excessive fat accumulation in the liver. One of the underlying pathophysiological mechanisms is insulin resistance (IR). Traditional Chinese medicine (TCM) has showed potential benefits in the management of NAFLD. Lingguizhugan decoction (LGZG) is a representative Chinese herbal formula; however, there is still no rigorous clinical trial supporting its application.

**Methods/design:**

This study will be a three-arm, dose-optimization, randomized, double-blinded, placebo-controlled clinical trial. A total of 243 patients with NAFLD will be recruited and randomly assigned to the standard dose LGZG (SLGD) group, low dose LGZG (LLGD) group, or the placebo group based on a ratio of 1:1:1. The treatment period will be 12 weeks and the follow-up period will last 4 weeks. The primary outcome will be the proportions of participants with at least a 1-unit decrease of HOMA-IR from baseline to 12 weeks. Secondary outcomes will include the changes of body weight, body mass index, liver function, blood lipid metabolism, blood glucose metabolism, inflammatory responses, liver-kidney echo ratio by ultrasound, and various scales. Biological samples will also be collected for future researches on mechanism exploration.

**Discussion:**

This study will provide initial evidence regarding the efficacy and safety of LGZG in the treatment of NAFLD with spleen-yang deficiency pattern and promote its application in community healthcare centers. In addition, potential mechanisms will be explored based on studies of oral and gut microbiota.

**Trial registration:**

Chinese Clinical Trial Registry, ChiCTR1800014364. Registered on 1 January 2018. The final protocol version was V3.0.

## Background

Non-alcoholic fatty liver disease (NAFLD) is one of the chronic liver diseases characterized by abnormal lipid accumulation in liver [1–3]. According to recent epidemiological studies, the prevalence of NAFLD is 25.24% worldwide and 27.37% in the Asia-Pacific region [4], while the prevalence in China is in the range of 24.47%–29.70% [5]. Although NAFLD shows no obvious clinical manifestations in the early stage, it is an important risk factor for various cardiovascular diseases, type 2 diabetes mellitus, and other metabolic diseases [6–8]. It has been reported that the all-cause mortality risk was also significantly elevated in a NAFLD population [9, 10].

The pathogenesis mechanism of NAFLD is still vague except that insulin resistance (IR) and genetic predisposition are relatively confirmed [11–13]. Generally based on disease progression, NAFLD can be divided into three stages, beginning from non-alcoholic fatty liver (NAFL), then to non-alcoholic steatohepatitis (NASH), and, finally, liver cirrhosis, which is a much greater risk factor for primary liver cancer [1, 14]. Therefore, how to prevent disease progression from potentially reversible NAFLD and NASH to irreversible cirrhosis is the key point for the treatment [15]. Currently, there are still no confirmed interventions for NAFLD [16]. In view of this, many patients will seek medical help from Traditional Chinese Medicine (TCM) in China.

Based on TCM theory, NAFLD belongs to the category of “Gan Pi,” and “phlegm dampness” and “phlegm fluid retention” are its pathological products. The basic pathogenesis of NAFLD is transportation dysfunction of the spleen due to deficiency of spleen yang [17, 18]. The corresponding TCM pattern is spleen-yang deficiency. Main clinical manifestations include laziness to speak, poor appetite, loose stool, cold limbs, and so on. The basic treatment principle is warming yang to promote diuresis [19, 20].

Lingguizhugan decoction (LGZG), first documented in the ancient classic “Jingui Yaolue,” is a representative formula under the principle of warming yang to promote diuresis. It is composed of *Poria* (Fulin), *Ramulus Cinnamomi* (Guizhi), *Rhizoma Atractylodis Macrocephalae* (Baizhu), and *Radix Glycyrrhizae* (Gancao) [21]. Previous studies showed that LGZG can significantly decrease triglycerides (TG) and lipid contents of the liver tissue, and improve hepatic injury in high fat diet-induced NAFLD rats [20, 22]. LGZG was also reported to be capable of alleviating IR in patients with diabetes [23]. However, there is still no high-level evidence to support LGZG application the in treatment of NAFLD. In addition, the dose of LGZG still follows the classic. Dose optimization will also be clinically significant due to the variation of environment and lifestyle.

Moreover, with the development of intestinal microbiota, many studies have verified the role of intestinal microbiota in the pathogenesis of NAFLD. Regulation of intestinal flora can increase appetite and energy intake in food, regulate gene expression regarding fat synthesis and beta oxidation, and improve IR [24–26]. These mechanisms may be involved in the occurrence of NAFLD. Other studies also reported that most gut microbiota originate from the oral cavity, then speculated that oral microbiota are also correlated to NAFLD [27, 28]. TCM may play an important role in treating diseases through regulating microbiota. Therefore, it will also be valuable to explore the potential mechanisms of LGZG against NAFLD from the research on oral and intestinal microbiota.

Hence, we designed this study to evaluate the efficacy and safety of LGZG for NAFLD with a spleen-yang deficiency pattern and to assess the optimal dosage. The results of this trial may help to establish the evidence base for the application of LGZG in community healthcare centers. In addition, the research of oral and gut microbiota will benefit the exploration of potential mechanisms.

## Methods/design

### Study design

The study protocol was approved by the Medical Ethics Committee of Longhua Hospital Affiliated to Shanghai University of Traditional Chinese Medicine (2017LCSY069) and registered in the Chinese Clinical Trial Registry (http://www.chictr.org.cn/edit.aspx?pid=24555&htm=4) with number ChiCTR1800014364 on 1 January 2018.

This study will be a 16-week, randomized, multi-center, double-blinded, three-arm, dose-optimization, placebo-controlled clinical trial. A total of 243 patients with NAFLD will be recruited through recruitment advertisements and introductions from doctors from three community healthcare centers in Shanghai, namely Zhangjiang community healthcare center, Beicai community healthcare center, and Sanlin community healthcare center. All three centers are based in Pudong New Area, Shanghai and no obvious difference will be supposed to exist in population and socioeconomic aspects. Eligible patients with NAFLD who agree to participate in the study will be randomly assigned to the standard dose Lingguizhugan decoction (SLGD) group, low dose Lingguizhugan decoction (LLGD) group, or the control group on a ratio of 1:1:1. On the basis of behavioral intervention therapy, patients in the SLGD and LLGD groups will be treated with different doses of LGZG; the control group will receive placebo. The LLGD group will be made of half of the standard dose, and the placebo will be one-tenth of the standard dose but with soluble starch, mixed colorant, and bitter component to achieve a comparable appearance, smell, and taste. The course of treatment will last 12 weeks. A 4-week follow-up will also be arranged to assess the continued effect. Participants will be assessed at week 0 (baseline), week 4, week 8, week 12 (end of treatment), and week 16 (end of follow-up). All participants will be asked to provide written informed consent before entering the trial. The study flow chart is shown in Fig. 1 and participant timeline is presented in Table 1. The Standard Protocol Items: Recommendations for Interventional Trials (SPIRIT) Checklist is presented in Additional file 1.

**Fig. 1 Fig1:**
[figure not shown]
*Flow chart* of the clinical study

**Table 1 Tab1:** Participant timeline

	Study phase					
	Screening	Allocation	Intervention			Follow-up
**Time point (weeks)**	**–2**	**0**	**4**	**8**	**12**	**16**
*Enrollment*						
Eligibility	**X**					
Informed consent	**X**					
**Allocation**		**X**				
*Intervention*						
SLGD			**X**	**X**	**X**	
LLGD			**X**	**X**	**X**	
Placebo			**X**	**X**	**X**	
*Assessment*						
Demographic indexes	**X**	**X**				
HOMA-IR		**X**	**X**		**X**	**X**
Hepatic function		**X**	**X**		**X**	**X**
Lipid metabolism		**X**	**X**		**X**	**X**
Glucose metabolism		**X**	**X**		**X**	**X**
Inflammation response		**X**	**X**		**X**	**X**
Liver-kidney echo ratio		**X**			**X**	
Body measurements		**X**	**X**	**X**	**X**	**X**
TCM pattern scale		**X**	**X**	**X**	**X**	**X**
SF-36		**X**			**X**	**X**
SAS		**X**			**X**	**X**
SDS		**X**			**X**	**X**
Vital signs		**X**	**X**	**X**	**X**	**X**
Blood routine test		**X**	**X**		**X**	**X**
Electrocardiograph		**X**	**X**		**X**	
AEs		**X**	**X**	**X**	**X**	**X**
Biological sample collection		**X**	**X**		**X**	**X**

*AE* adverse event, *LLGD* low dose Lingguizhugan decoction, *SLGD* standard dose Lingguizhugan decoction

### Participants

#### Diagnostic criteria

All participants should meet the diagnostic criteria of NAFLD and TCM pattern differentiation criteria of spleen-yang deficiency. Diagnostic criteria of NAFLD will be based on the American Association for the Study of Liver Diseases (AASLD) in 2017 [12]. To be specific, the following four criteria should all be met: (a) imaging (ultrasound, computed tomography, or magnetic resonance imaging) or histological evidence of hepatic steatosis; (b) no significant alcohol consumption, defined as > 21 standard drinks per week in men and > 14 standard drinks per week in women; (c) exclusion of other reasons inducing hepatic steatosis, including but not limited to hepatitis C, specific drugs induced, parenteral nutrition, and severe malnutrition; and (d) no coexistence of other chronic liver disease, including but not limited to hemochromatosis, autoimmune liver disease, chronic viral hepatitis, alpha-1 antitrypsin deficiency, hepatolenticular degeneration, and drug-induced liver disease.

The TCM pattern differentiation criteria of spleen-yang deficiency will refer to the expert consensus of spleen deficiency by China Association of Traditional Chinese Medicine in 2017, previous systematic review, and the clinical guidelines for the new Chinese medicine [29–31]. Ten symptoms and signs will be assessed by continuous 100-point scale, a higher score means a more severe degree. Every symptom or sign possesses with a certain weight. The scoring will be calculated through multiplying the rating score by the weight. Spleen-yang deficiency pattern will be defined as total score of 10 dimensions ≥ 20. The detailed rating scale is shown in Table 2.

**Table 2 Tab2:** Spleen-yang deficiency pattern scale

Symptoms	Score (0–100)
Do you feel too lazy to speak?	20%
Do you sweat often or have night sweats even though you are not active and it is not hot?	5%
Do you have bland and tasteless feeling in your mouth?	10%
Does your stool have a thin texture and is loose?	20%
Do you feel more saliva?	10%
Do you have bleeding gums?	5%
Do you feel a lack of warmth in the extremities	10%
Do you have insomnia/trouble sleeping at night?	5%
Are you likely to catch a cold?	10%
Do these symptoms affect your eating habits (such as hate greasy good)?	5%
Total	

#### Inclusion criteria

Participants who meet all of the following criteria will be included: (a) aged 18–80 years, men or women; (b) confirmed diagnosis of NAFLD; (c) confirmed diagnosis of spleen-yang deficiency pattern; and (d) voluntary informed consent and agreement to participate in every visit, examination, and treatment according to the protocol.

#### Exclusion criteria

Participants who meet any of the following criteria will be excluded: (a) combination with other specific liver diseases which would induce fatty liver, including but not limited to alcoholic liver disease, chronic hepatitis C, autoimmune liver disease, and hepatocellular degeneration; (b) fatty liver induced by drugs (e.g. tamoxifen, ethylamine iodifurone, valproate, methotrexate, glucocorticoid), total parenteral nutrition, inflammatory bowel disease, hypothyroidism, Cushing syndrome, abetalipoproteinemia, and other syndromes related to insulin-resistance (e.g. lipid atrophic diabetes, Mauriac syndrome); (c) combination with serious primary diseases and mental diseases, including but not limited to cardiovascular and cerebrovascular diseases, hepatic diseases, renal diseases, hematologic diseases, cancers, and schizophrenia; (d) combination with diabetes or currently receiving anti-diabetic medicine treatment; (e) currently receiving treatments for NAFLD (including Chinese herbal decoction, Chinese patent medicine, and chemical agents); (f) antibiotics administration in the last month; (g) allergy to compositions of experimental agents or possessing an allergic constitution; (h) pregnancy and lactating women, and women who are likely to be pregnant but refuse to keep predefined contraception measures during the study; (i) participation in other clinical trials in the last 3 months or currently joining other trials; (j) mental or legal disability; (k) cannot obey medical advice for therapeutic lifestyle modifications; and/or (l) suspicious of drug abuse or possessing other forbidden criteria.

### Interventions

All clinical investigators responsible for diagnosis and treatment will be registered practitioners of TCM. Before the start of the trial, a 3-day training session will be held for all clinical investigators involved in the study. All participants with NAFLD will receive treatment for 12 weeks according to the random assignment. LGZG has been utilized for a long time in clinical practice. Participation in this trial will not anticipate bringing any harm to the patients. Hence, no post-trial care will be arranged.

#### Behavioral intervention

Behavioral interventions will be given to all three groups and the prescription will be based on the Guidelines for Prevention and Control of Overweight and Obesity in Chinese Adults [32]. In brief, participants will be required to limit calorie intake (approximate 1660 kcal per day) and guarantee physical exercises (moderate aerobic exercise at least 150 min per week). Individuals will be asked to complete daily dietary and exercise records during treatment (Additional file 2).

#### Drug intervention

LGZG is a traditional formula which is composed of *Poria* (Fulin), *Ramulus Cinnamomi* (Guizhi), *Rhizoma Atractylodis Macrocephalae* (Baizhu), and *Radix Glycyrrhizae* (Gancao). The standard dose for each herb is 12 g, 9 g, 6 g, and 6 g, respectively. The LLGD group will be made of half of the standard dose and the placebo will be one-tenth of the standard dose. The course of treatment lasts 12 weeks. Participants will be required to take one dosage (one pack) of granules 30 min after breakfast, once daily on weekdays. A total of 60 packs per patient will be administrated. The granules used in this study will be produced by Sichuan Neo-green Pharmaceutical Technology Development Co., Ltd. (Sichuan, China). The crude herbs will be extracted and made into granules. The production process will be under the standard of Good Manufacturing Practice. No significant difference was found among granules samples from the three groups in terms of color, appearance, shape, smell, and weight (Fig. 2).

**Fig. 2 Fig2:**
[figure not shown]
Appearance of drug samples from three groups

#### Concomitant treatment regulations

Except for research products, other drugs (including Chinese herbal decoctions, Chinese patent drugs, and chemical drugs) and interventions (including acupuncture, cupping, and massage) that may interfere with the trial will be forbidden during the study. For participants with other existing diseases who cannot stop relevant therapies should record concomitant interventions in detail. If the disease progresses during the study period, patients can withdraw from the study and use other treatment methods. The case will be regarded as invalid and the patient will be required to complete the relevant examinations and evaluations as much as possible.

#### Drug dispensation and compliance assessment

Drugs will be packed as required in the double-blinded study. During the treatment period, a certain amount of packs will be distributed in week 0, week 4, and week 8 (22 packs). The two additional packs will be reserved for unforeseen circumstances. After taking the medicine, the patients will be asked to return all the remaining products and packages at their next visit. The clinical investigators will count the number of remaining products and calculate the participants’ compliance. The research team will establish a WeChat group for health guidance and periodically contact individuals by telephone or WeChat to check safety and improve compliance.

### Outcome measures

The schedule for all outcome measures is shown in Table 1. All demographic data will be determined before treatment, including the date of birth, gender, body weight, height, medication history, past medical history, smoking and drinking status, and course of disease.

The primary outcome will be the proportion of participants with at least a 1-unit decrease of HOMA-IR from baseline to treatment endpoint (week 12) [33]. Secondary outcomes will include body measurements (body weight and body mass index), hepatic function (alanine aminotransferase [ALT], aspartate transaminase [AST], gamma-glutamyl transpeptidase [GGT], and alkaline phosphatase [ALP]), lipid metabolism profiles (total cholesterol [TC], TG, low-density lipoprotein cholesterol [LDL-C], high-density lipoprotein cholesterol [HDL-C], apolipoprotein A [apoA], apolipoprotein B [apoB], and non-high-density lipoprotein cholesterol [non-HDL-C]), glucose metabolism profiles (fasting blood glucose [FPG], fasting insulin [FINS], and glycosylated hemoglobin [HbA1c]), inflammatory responses (white blood cell [WBC] counts, C-reactive protein [CRP], and inflammatory cytokines), liver-kidney echo ratio by ultrasound, and scorings of various questionnaires (TCM spleen-yang pattern scale, the MOS item short from health survey [SF-36], self-rating depressive scale [SDS], and self-rating anxiety scale [SAS]). All secondary outcomes will also be evaluated from baseline to treatment endpoint.

Safety variables will include vital signs (including blood pressure, respiratory, heart rate, and body temperature) evaluated at every visit, electrocardiogram (ECG) and blood tests (including blood routine test and renal function) evaluated at baseline, week 4, and week 12. Adverse events (AEs) will be observed and recorded throughout the whole trial. LGZG is a classical herbal formula and has satisfactory safety profiles. Potential AEs may be mild gastrointestinal reactions, which will be alleviated spontaneously without any additional medical interventions. Clinical investigators should document any AEs in a case report form (CRF), including the following information: occurrence time; symptoms and signs; severity; duration; laboratory examinations; interventions; outcomes; and follow-up time. If an AE occurs, clinical investigators should adopt appropriate measures to guarantee the safety of participants based on the actual situation. If serious AEs occur, clinical investigators should inform the principal investigator within 2 h of the event. The principal investigator should then report to the Medical Ethics Committee and Data Monitoring Committee (DMC) within 24 h. It will be decided whether to terminate the trial after a discussion.

### Biological sample collection

In order to further explore the mechanism of LGZG on NAFLD and its effect on oral and gut microbiota, biological samples will be collected in the present study. On the consent form, the collection of biological samples will be clearly stated and the participants will have the right to refuse to provide biological samples. All biological specimens will be used for auxiliary researches in the future. Blood samples will be planned for subsequent DNA methylation and metabonomics studies. Feces and coating on the tongue will be planned for gut and oral microbiota studies. Whole blood, morning urine, feces, and coating on the tongue will be collected at baseline, 4 weeks, 12 weeks, and 16 weeks. All samples will be transferred and stored in a refrigerator at 80 °C within 24 h.

### Sample size estimation

Sample size was estimated based on the clinical primary outcome. As far as we know, this is the first RCT evaluating the efficacy of LGZG versus placebo. No data are available as a reference. Therefore, based on our previous animal studies and consultation with TCM experts, we assumed that the effect size for the SLGD group is 30%, LLGD group is 15%, and placebo group is 10%. If α = 0.05 and β = 0.10, the sample size can be calculated by the following formula:
$$ \mathrm{n}=\frac{1641.4\lambda }{{\left({\sin}^{-1}\sqrt{p_{max}}-{\sin}^{-1}\sqrt{p_{min}}\right)}^2} $$

The λ is the degree of freedom, taking 12.65 in this case. The p_max_ is 30% and the p_min_ is 10%. Assuming the maximum dropout rate is 20%, 81 patients will be required for each group, with a total of 243 patients.

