### Statistical analysis

The analysis of efficacy and safety will be based on the principle of intention-to-treat (ITT), namely all randomized participants will enter the final analysis. The missing value will be filled by the method of the last observation carried forward. Data will be presented as mean with standard deviation, median with range, or number with percentage. Data analysis will use the SPSS 19.0 for Window software. All statistical inferences will be performed using a two-sided test with a statistically significant test level of *P* < 0.05 and the confidence interval of parameters will be estimated by 95% confidence interval. Differences within groups will be assessed by paired t-test, chi-square test, or Wilcoxon signed rank test according to specific variables. Differences between groups will be assessed by one-way analysis of variance or Kruskal–Wallis test based on characteristics of data. Post-hoc pairwise multiple comparisons will be performed if statistical significance is found.

No interim analysis was arranged in this trial due to a short intervention period and safety profiles of LGZG. Potential sub-group analyses will be determined based on characteristics of included participants, for instance, different categories of body mass index and different combined diseases.

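### The printed sample-size formula gives 96 evaluable patients per group (119–120 with 20% dropout), not 81; for the three-group test it sizes, 81 gives about 84–88% power if all are analysed, not 90%

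*Protocol article*

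**What the plan says.** All inputs stand in the protocol article under Sample size estimation. The error rates are set by "If α = 0.05 and β = 0.10, the sample size can be calculated by the following formula". The assumed response rates appear as "we assumed that the effect size for the SLGD group is 30%, LLGD group is 15%, and placebo group is 10" (per cent). The formula is n = 1641.4λ divided by the squared difference of the arcsine-root-transformed largest and smallest proportions, 30% and 10%. On λ the text says "The λ is the degree of freedom, taking 12.65 in this case". It ends with "Assuming the maximum dropout rate is 20%, 81 patients will be required for each group, with a total of 243 patients". No evaluable number before dropout is given.

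The total is repeated in the Abstract ("A total of 243 patients with NAFLD will be recruited and randomly assigned") and under Study design. Under Statistical analysis the tests are two-sided at 5% ("All statistical inferences will be performed using a two-sided test with a statistically significant test level of" P < 0.05). Everyone randomised is analysed, with missing values filled by last observation carried forward (LOCF). Pairwise comparisons follow only after a significant overall result.

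**The concern.** Every input to a closed formula is printed, so the result can be checked directly, and it does not come out. The stated number per group, which is meant to contain a dropout allowance, is smaller than the formula's result with no allowance at all. This paragraph is the only justification for 243 patients, and it carries the claim of 90% power for the primary outcome. If the claim stays, a null result will be read as coming from a trial with a 10% chance of missing the assumed effect. For the planned three-group test that chance is larger.

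**Working it through.** **Inputs.** λ = 12.65, p_max = 0.30, p_min = 0.10, α = 0.05, β = 0.10, dropout 20% (Sample size estimation). Two-sided testing, all randomised analysed, LOCF (Statistical analysis). The constant 1641.4 equals 0.5 × (180/π)², so the angles are in degrees.

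**Step 1: the plan's own formula.**
- arcsin √0.30 = 33.211°; arcsin √0.10 = 18.435°.
- Difference 14.776; squared 218.33.
- n = 1641.4 × 12.65 / 218.33 = 20,763.7 / 218.33 = 95.1, so 96 evaluable per group.

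**Step 2: dropout.**
- 95.1 / 0.8 = 118.9, so 119 per group (357 in total). Rounding to 96 first gives 96 / 0.8 = 120 (360 in total).
- The cruder multiplication by 1.2 gives 114.1 or 115.2, so 115–116 per group.
- The stated figure of 81 is not reproduced. It is already below 95.1.

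**Step 3: is λ a misprint?** Solving the noncentral chi-square with 2 degrees of freedom at α = 0.05 gives λ = 12.654 for 90% power and 9.635 for 80%. So 12.65 is the right value for the stated β and three groups. It is the noncentrality parameter; the degrees of freedom are 2. Working backwards, 81 × 0.8 = 64.8 evaluable implies λ = 64.8 × 218.33 / 1641.4 = 8.62, below even the 80% value.

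**Step 4: can another calculation give 81?**

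| Calculation (30% vs 10%, two groups) | n per group | With dropout | Conflict with the article |
|---|---|---|---|
| Arcsine, one-sided, 90% | 64.4 | /0.8 = 80.5, so 81 | two-sided testing; λ |
| Pooled proportions, one-sided, 90% | 67 | ×1.2 = 80.4, so 81 | two-sided testing; λ |
| Arcsine, two-sided, 85% | 67.5 | ×1.2 = 81.0 | β = 0.10; λ |
| Arcsine or pooled, two-sided, 90% | 79 or 82 | none added | the 20% allowance; λ |

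**Step 5: power that 81 per group gives.** For the three-group test, power = P(χ²(2 df, noncentrality) > 5.991). In the formula's configuration, which uses only the two extreme proportions, the noncentrality is n × 218.33 / 1641.4. For the chi-square test at 30/15/10% the mean is 0.1833, the sum of squared deviations 0.02167, and the noncentrality n × 0.02167 / (0.1833 × 0.8167) = 0.1447n.

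| Three-group test, 5% | 65 evaluable | 81 analysed | 96 analysed |
|---|---|---|---|
| Formula's configuration | 75.3% | 84.5% | 90.3% |
| 30/15/10%, arcsine | 77.7% | 86.5% | 91.8% |
| 30/15/10%, chi-square | 79.0% | 87.5% | 92.6% |
| 30/15/10%, simulated (400,000 runs) | 78.1% | 87.1% | 92.1% |

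At 30/15/10% the chi-square test needs 12.654 / 0.1447 = 87.4, so 88 evaluable per group for 90% power, or 88 / 0.8 = 110 with dropout (330 in total).

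| Standard dose vs placebo, two-sided | 65 evaluable | 81 analysed |
|---|---|---|
| Unadjusted 0.05, pooled / arcsine | 82.1% / 83.7% | 89.7% / 90.7% |
| Bonferroni 0.05/3, pooled / arcsine | 68.1% / 70.8% | 79.2% / 81.3% |

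The article names no multiplicity method, so Bonferroni for three comparisons is an assumption.

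**The case against.** The best defence is that the analysis set is everyone randomised, with LOCF, so all 81 per group count. On that footing a plain test of standard dose against placebo, which is the 30% versus 10% contrast in the formula, has 89.7–90.7% power. This stands. A reader might infer that 90% is missed whichever way the trial is analysed; the article does not support that. The defence does not rescue the paragraph, however. The formula and λ size a three-group test, pairwise tests come only after it, and the 90% disappears once the pair is adjusted for three comparisons. It also assumes that dropouts respond at the assumed rates.

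Three further inferences go too far:
- **75–79% as the trial's power.** That needs 65 evaluable per group, which is not the stated analysis set. It is a completers-only sensitivity case.
- **76% with all 81 analysed.** This follows if all dropouts (20%) become non-responders (24/12/8%). The article does not say so, and Table 1 schedules HOMA-IR at week 4, so LOCF could carry a response forward.
- **A shortfall of 114 patients (357 − 243).** That measures the gap to the formula's conservative configuration. At 30/15/10% the gap is 330 − 243 = 87.

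The article also cannot show where the error lies. 81 may come from another calculation, with the formula or λ misreported.

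**Conclusion.** The point holds. The stated 81 per group does not follow from the stated formula under any dropout convention. For the three-group comparison that the formula sizes, the chance of missing the assumed effect is about 12–16% with all 81 analysed (power 84–88%), and about 21–25% with completers only (power 75–79%), against the stated 10%. On the stated analysis set the loss of power is therefore about 2 to 6 percentage points: real, but moderate. These figures rest on the article's assumed 30/15/10% rates or the formula's two-extreme configuration, and the all-analysed figures on dropouts responding at those rates. Calling λ the degree of freedom is a separate labelling error. Neither error affects the type I error rate or the estimates. What is affected is how a null result may be read.

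**What to change.** Rewrite the paragraph under Sample size estimation:
- Reconcile the formula, λ and 81, and state the calculation actually used. If it was the printed formula, report 96 evaluable per group and 119 or 120 with dropout, with one rounding convention throughout.
- Call λ the noncentrality parameter for 2 degrees of freedom.
- Replace the 90% claim with the power of 81 per group for the three-group comparison: 84–88% with all analysed, 75–79% for completers only, with the assumptions stated.
- If the roughly 90% for standard dose versus placebo is quoted, say that it is unadjusted and has all 81 analysed, and give the 79–81% under Bonferroni beside it.
- Interpret a null result against the restated power.

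The cost is a correction to the text. Trial status reports recruitment complete in February 2019 and data locked in June 2019, so no patients are added. The only downside is a less favourable stated power.
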